## Discussion

This study aims to evaluate the Habit-based Sleep Health Intervention (HABITs) and whether adding a text message intervention helps young adults to form habits that modify the psychosocial and behavioral contributors to eveningness. By integrating the science on habits and learning theory with behavior change interventions, the aim is to help recipients turn new behaviors into habits and thereby increase the benefits of the intervention in both the short and longer term [42]. Additionally, the text message intervention has great potential because it is a low-cost, efficient, and potent intervention that may help habit formation and bolster the maintenance of behavior change [62–64]. We will investigate if this approach improves the utilization of sleep health behaviors, sleep health behavior habits, sleep and circadian functioning, and functioning in five health-relevant domains.

The findings have the potential to advance knowledge and address several research areas and priorities. First, this study will demonstrate whether leveraging the science of habits can be translated into effects on sleep and circadian functioning and health-relevant outcomes. Importantly, the habit formation approach is potentially “transdiagnostic” (relevant to a broad range of problems) and “pantreatment” (relevant to a broad range of types of treatment) [42]. Thus, evaluating this strategy may help other scientists improve interventions and outcomes for a variety of populations and settings. Second, this study will contribute to literature evaluating the use of a low-cost and efficient text message intervention, grounded in learning theory, to bolster habit formation and maintenance. Third, by focusing on participants with an eveningness chronotype, the present study will add to the literature on how addressing eveningness may improve outcomes in the short and longer term. The latter is particularly important given eveningness’ adverse health consequences and the limited research on interventions to address it. Fourth, this study will contribute to knowledge on the processes of behavior change during emerging adulthood, which is often marked by a shift in priorities toward self-sufficiency and personal responsibility. Therefore, advancing the understanding of processes related to the formation and maintenance of helpful behaviors is particularly important for the developmental period spanned by the study sample.

These potential contributions should be considered alongside the protocol’s methodological limitations. First, for assessing the five health-relevant domains, an extensive search of health measures (e.g., SF-36, PhenX, WHODAS, PROMIS, neuro-QL, BRIEF, GHQ) resulted in no single measure that covered all five health domains in a developmentally appropriate way. Hence, the Work and Social Adjustment Scale [87] was adapted to serve as a single measure assessing the five health domains (Adapted WSAS). In addition to the Adapted WSAS, each domain will be assessed with a different measure and through the EMA Composite Risk Score. These measures will also function as a measure of convergent validity when assessing the psychometric properties of the Adapted WSAS, which will be reported in a supplement to the main report. Second, as there is evidence that the large age range of participants (18–30 years of age) and sex can impact sleep and/or intervention outcomes [114, 115], the content and implementation method for HABITs will be adapted [125–127] by the sleep coach, with careful training and supervision, using an individualized case formulation [76] to determine the amount of time spent on each component and the style of delivering each component. Third, adding a placebo text arm to control for receiving a text was considered. However, the pilot study and focus groups indicated that placebo texts detracted from habit formation and were “annoying” to the participants. Additionally, including a placebo text arm would require a larger sample and more resources.

In sum, this study has the potential to advance knowledge on: (a) the value of leveraging the science of habits and learning theory in behavior change interventions, (b) the use of a low-cost and efficient text-based intervention for habit formation and maintenance, (c) interventions addressing eveningness and the impact on a range of outcomes, and (d) processes related to behavior change during an important and understudied stage of development (i.e., emerging adulthood).

## Trial status

Protocol version 1, December 9, 2021. Data collection started in May 2022 and will continue through July 2026. Recruitment started in May 2022 and is projected to finish in December 2025.

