## Aims

This randomized controlled two-arm parallel group superiority study with 1:1 allocation ratio will be conducted with young adults who are 18–30 years of age, exhibit an eveningness chronotype, and demonstrate elevated symptoms in one of the five health domains. Participants will be randomized (1:1) to HABITs alone or HABITs plus Text Message Intervention (HABITs + Texts). There are three aims.

Aim 1 is to assess if adding a text message intervention to HABITs improves sleep health behaviors in the short (post-treatment) and longer term (6-month and 12-month follow-up), relative to HABITs alone. Hypothesis 1 is that, relative to HABITs, participants in HABITs + Texts will (a) report utilizing more sleep health behaviors and (b) establish stronger sleep health behavior habits. We hypothesize that these effects (1a and 1b) will be observed from pre-treatment to post-treatment, pre-treatment to 6-month follow-up, and pre-treatment to 12-month follow-up.

Aim 2 is to assess if adding a text message intervention to HABITs improves sleep and circadian functioning in the short (post-treatment) and longer term (6-month and 12-month follow-up), relative to HABITs alone. Hypothesis 2 is that, relative to HABITs, participants in HABITs + Texts will exhibit improved sleep and circadian functioning. We hypothesize that this effect will be observed from pre-treatment to post-treatment, pre-treatment to 6-month follow-up, and pre-treatment to 12-month follow-up.

Aim 3 is to assess if adding a text message intervention to HABITs improves functioning in the five health-relevant domains in the short (post-treatment) and longer term (6-month and 12-month follow-up), relative to HABITs alone. Hypothesis 3 is that, relative to HABITs, participants in HABITs + Texts will exhibit lower health risk. We hypothesize that this effect will be observed from pre-treatment to post-treatment, pre-treatment to 6-month follow-up, and pre-treatment to 12-month follow-up.

As an Exploratory Aim 1, comparing HABITs and HABITs + Texts, we will examine (a) if the strength of sleep health behavior habit formation mediates the effects of the intervention (specifically by adding the text intervention to HABITs) on improvement in sleep and circadian outcomes, and health-relevant domain outcomes, and (b) if intervention effects are moderated by selected variables (i.e., age, sex, and socioeconomic status).

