### Measures

In addition to the measures below, a sociodemographics form is completed by participants at the pre-treatment assessment. Only measures that will be analyzed for the main aims of the study are reported below (see Aims section). The schedule for administering the measures is in Table 4. Unless otherwise specified, the measures below will be administered at the pre-treatment, post-treatment, 6-month follow-up, and 12-month follow-up assessments. To see which measure is associated with each outcome (i.e., utilization, habits, sleep and circadian functioning, and health-relevant domains) see Table 5.

**Table 4 Tab4:** Timeline of measures

		**Pre-treatment**	**Treatment**	**Post-treatment**	**6-month follow-up**	**12-month follow-up**
	Sociodemographics	X				
**Primary**	Utilization Scale	X		X	X	X
	SRBAI-US	X		X	X	X
	CSHS	X		X	X	X
	CSM	X		X	X	X
	PROMIS-SRI	X		X	X	X
	PROMIS-SD	X		X	X	X
	Adapted WSAS Total Score	X		X	X	X
**Secondary**	Adapted SRHI – Primary Bundle		X	X	X	X
	PSQI	X		X	X	X
	Sleep Diary^a^	X	X	X	X	X
	Actigraphy^a^	X		X		
	DASS	X		X	X	X
	PROMIS-CF	X		X	X	X
	BSSS	X		X	X	X
	PROMIS-APS	X		X	X	X
	PHQ	X		X	X	X
	EMA Composite Risk Score^b^	X		X		
**Other**	Adapted SRHI – Secondary Bundle		X	X	X	X
	Adapted WSAS^c^	X		X	X	X
	Sleep Diary^d^	X	X	X	X	X
	Actigraphy^e^	X		X		
	Adapted Authenticity Scale	X		X	X	X
	Adapted CEQ^f^		X			
	Adverse Events Checklist			X		
	Proportion of Text Messages Read^g^		X			

*Note.* SRBAI-US Adapted Self-Report Behavioral Automaticity Index integrated with the Utilization Scale , CSHS Composite Sleep Health Score, CSM Composite Scale of Morningness, PROMIS-SRI PROMIS Sleep-Related Impairment Scale, PROMIS-SD PROMIS Sleep-Disturbance Scale, Adapted WSAS Adapted Version of the Work and Social Adjustment Scale, Adapted SRHI – Primary Bundle Adapted Self-Report Habit Index – Primary Bundle to Build, PSQI Pittsburgh Sleep Quality Index, DASS Depression, Anxiety, and Stress Scales, PROMIS-CF PROMIS-Cognitive Function Scale, BSSS Brief Sensation Seeking Scale, PROMIS-APS PROMIS-Ability to Participate in Social Roles & Activities Scale, PHQ Physical Health Questionnaire, EMA Ecological Momentary Assessment, Adapted SRHI – Secondary Bundle Adapted Self-Report Habit Index – Secondary Bundle to Build, Adapted CEQ Adapted Credibility Expectancy Questionnaire

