### Procedure

We will recruit participants within the USA and Canada, with by far the most participants from the former. Recruitment efforts will include distribution of information about the study to doctors and health care clinics as well as advertisements in the community (e.g., outpatient medical and mental health clinics in the San Francisco Bay Area) and online (e.g., Facebook, Reddit, and Instagram). People who are interested in learning more will be directed to contact the UCB research staff directly by phone or email.

Prospective participants will verbally consent to an initial eligibility phone screen. If the participant is eligible to participate in the full study, they will be invited to the pre-treatment assessment. Informed consent will be obtained prior to starting the pre-treatment assessment via HIPAA-compliant DocuSign, mail, or in-person, if the participant prefers. The pre-treatment assessment will be completed virtually (i.e., phone or HIPAA-compliant Zoom). Informed consent and assessments will be conducted by assessors (i.e., UCB research staff). Assessors enter anonymized data collected from the pre-treatment assessment via a HIPAA-compliant Qualtrics survey.

Once the participant is enrolled, they will be randomly allocated to HABITs or HABITs + Texts (see Allocation section for more details). Both intervention arms include HABITs, which involve three 50-min individual weekly sessions followed by six 30-min individual weekly sessions. Sessions are completed virtually via HIPAA-compliant Zoom. Treatment is delivered by sleep coaches (i.e., UCB research staff who are trained and supervised by [name], [name], MD, and [name]). Only the HABITs + Texts group will receive the text messaging intervention. Text messages will be delivered for 6 weeks. The text messages are collaboratively written by the participant and the participant’s sleep coach (and reviewed and approved by [name] or MD). During treatment, sleep coaches will assist participants in completing treatment assessments using HIPAA-compliant Qualtrics.

At the conclusion of treatment, typically within 8–11 weeks, the post-treatment assessment will take place within 2 weeks of the final session. The follow-ups will take place 6 months and 12 months after the pre-treatment assessment. The post-treatment assessment, 6-, and 12-month follow-ups will be completed by assessors via phone or HIPAA-compliant Zoom, and anonymized data will be entered via HIPAA-compliant Qualtrics.

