## Planned analyses

### Preliminary analyses and missing data

Data will be audited for quality and completeness. Missing or aberrant data will be verified for maximal data integrity. We will evaluate the distributions of the outcome variables and ensure that all the assumptions of planned analyses (e.g., linearity, normally distributed residuals) are met.

As per the power analysis described, we plan to recruit 160 participants, which allows for 20% attrition. Intent-to-treat analyses will use all available data via maximum likelihood estimation and produce valid inferences if attrition depends on intervention group or on previous outcomes for the same participant [118]. Additionally, sensitivity analyses may be conducted using multiple imputation to address missing data (e.g., dropouts, every item is not completed). If dropout is related to other variables, they will be included as predictors in the model to reduce any bias due to non-random missing data.

For Aims 1–3, all models will control for stratification factors (i.e., sex, age) used during the randomization procedure. Prior to the main analyses, appropriate statistical tests will be used to examine pre-treatment (i.e., baseline) differences between groups (e.g., education, current living arrangement, relationship status) to ensure comparability of the two randomized conditions (HABITs vs. HABITs + Texts) at pre-treatment and adequacy of the randomization. These tests will not be used to select covariates in the intent-to-treat analysis [119]. Instead, the potential influences of pre-treatment differences will be evaluated as moderators (described below in Exploratory Aim 1).

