### Aims 1–3: Effectiveness outcomes of HABITs versus HABITs + Texts

For Aims 1–3, we will use intent-to-treat analyses, including all randomized participants as randomized in the analysis regardless of their adherence or completion of the assigned intervention. We will use multilevel modeling [120] to account for multiple observations over time (pre-treatment, post-treatment, 6-month, and 12-month follow-up) nested within participants. The level 1 equation captures within-person variation across time and will include dummy-coded time indicators (0 = pre-treatment, 1 = post-treatment, 2 = 6-month follow-up, 3 = 12-month follow-up) as predictors. The level 2 equation captures between-person variations in the intercept and slope of time and will include dummy-coded intervention condition (0 = HABITs, 1 = HABITs + Texts) and intervention-by-time interaction terms, as predictors. The parameters of interest will be significant intervention-by-time interactions at the 5% level (i.e., differences in intervention effects on change in outcomes from pre-treatment to post-treatment, pre-treatment to 6-month follow-up, and pre-treatment to 12-month follow-up). Significant intervention-by-time interactions indicate that the trajectory of change on outcomes is significantly different over time, comparing HABITs + Texts to HABITs. For Aim 1a, utilization of sleep health behaviors, as indexed by the Utilization Scale will be modeled as the continuous outcome variable. For Aim 1b, sleep health behavior habits, as indexed by the primary measure (SRBAI-US), secondary measure (Adapted SRHI – Primary), and other measure (Adapted SRHI – Secondary), will be modeled as the continuous outcome variables, separately. For Aim 2, sleep and circadian functioning, as indexed by primary measures (i.e., CSHS, CSM, PROMIS-SRI, and PROMIS-SD) and secondary measures (i.e., PSQI, Sleep Diary and Actigraphy [night-to-night variability in the mid-point of sleep]) will be modeled as the continuous outcome variables, separately. For Aim 3, the latent variables of health risk, as indexed by the primary measure (Adapted WSAS) and secondary measures (i.e., DASS, PROMIS-CF, BSSS, PROMIS-APS, PHQ, and EMA Composite Risk Score^8^), will be modeled as the continuous outcome variables, separately.

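### The stated end of data collection (July 2026) is inconsistent with recruitment to December 2025 and a 12-month follow-up timed from the pre-treatment assessment

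*Protocol article*

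**What the plan says.** The Trial status section gives two calendar limits in adjoining sentences. It says that data collection "will continue through July 2026. Recruitment started in May 2022 and is projected to finish in December 2025".

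The Procedure section fixes the clock for follow-up: "The follow-ups will take place 6 months and 12 months after the pre-treatment assessment". The Measures section sets the default schedule: "the measures below will be administered at the pre-treatment, post-treatment, 6-month follow-up, and 12-month follow-up assessments". Table 4 lists every primary measure at 12 months.

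The 12-month visit carries hypotheses. Aim 1 asks whether adding texts "improves sleep health behaviors in the short (post-treatment) and longer term (6-month and 12-month follow-up), relative to HABITs alone", and Aims 2 and 3 use the same timepoints. The analysis section for Aims 1–3 takes as its parameters of interest the intervention-by-time interactions for "pre-treatment to post-treatment, pre-treatment to 6-month follow-up, and pre-treatment to 12-month follow-up). Significant intervention-by-time interactions indicate" a different trajectory between arms.

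On losses, the section on preliminary analyses and missing data says "we plan to recruit 160 participants, which allows for 20% attrition". The Sample size section gives 128 participants as the number needed, before inflation to 160.

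**The concern.** Recruitment that ends in December 2025 needs 12-month data collection until about December 2026. The article stops data collection in July 2026. It does not shorten follow-up for late enrolees, set an earlier last enrolment date, or mention administrative censoring. The only follow-up data it drops at 6 and 12 months are the EMA data (Changes to preregistration).

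Longer-term maintenance is the rationale of the trial. The Background cites low use of the sleep health behaviors at 6 and 12 months in earlier work as the reason for adding habit science. If both dates are kept, the 12-month contrast loses participants by calendar, on top of an attrition allowance that the step from 160 to 128 already uses in full.

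**Working it through.** **Inputs from the article.** Recruitment May 2022 to December 2025; data collection to July 2026 (Trial status). 12-month visit counted from the pre-treatment assessment (Procedure). N = 160, 128 needed, d = 0.60, two-tailed alpha 0.05 with 0.017 per aim, 20% attrition (Sample size). 1:1 allocation (Allocation). The accrual rate is not given.

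**The plan's own figures.** 128 / (1 − 0.20) = 160, so the total reproduces. A two-sample t-test with d = 0.60 and two-sided alpha 0.017 needs about 119 participants for 80% power (120 with equal arms). At 128 the power is 83%, so 128 has some slack on those inputs.

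**Calendar.**
- Last 12-month visit: December 2025 + 12 months = December 2026. Gap to July 2026: 5 months.
- Latest pre-treatment assessment that allows a 12-month visit: July 2026 − 12 months = July 2025.
- Last 6-month visit: December 2025 + 6 months = June 2026, inside the stated period. Only the 12-month visit is lost.

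**Number affected.** Recruitment spans 44 calendar months, counted inclusively. August to December 2025 is 5 of them, which leaves 39. If accrual in those 5 months runs at r times the earlier rate, the number affected is 160 × 5r / (39 + 5r).
- r = 0.5: 160 × 2.5 / 41.5 ≈ 10
- r = 1 (even accrual): 160 × 5 / 44 ≈ 18, or 11%
- r = 2: 160 × 10 / 49 ≈ 33

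**Remaining at 12 months**, with 20% attrition applied to the rest, and power of a two-sample t-test for d = 0.60:

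| Late accrual (r) | Affected | With 12-month data | Missing at 12 months | Power, alpha 0.017 |
|---|---|---|---|---|
| No calendar loss | 0 | 128 | 20% | 83% |
| 0.5 | 10 | (160 − 9.6) × 0.8 ≈ 120 | 25% | 81% |
| 1 | 18 | (160 − 18.2) × 0.8 ≈ 113 | 29% | 78% |
| 2 | 33 | (160 − 32.7) × 0.8 ≈ 102 | 36% | 73% |

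At the 5% level named in the analysis section, power for d = 0.60 at the even-accrual n is about 89%.

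**The case against.** The date conflict itself is hard to contest. Five months is too long for month rounding, and timing follow-up from the end of treatment would widen the gap. The objections concern what follows from it.

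- **Which date is wrong.** A reader might infer that everyone enrolled after July 2025 will have no 12-month assessment. That follows only if both dates are right. The recruitment date is expressly a projection, and a slip or an outdated forecast in either date fits the text equally well. This objection stands: what the article shows is an inconsistency, not a decision to drop visits.
- **Power.** A reader might also infer that the 12-month contrast falls below the 80% target. That depends on accrual, which the article does not give. At half-rate late accrual, about 120 remain and power stays just above 80%; with even accrual it is two points short. At the 5% level it stays near 89%. A t-test on participants with 12-month data also ignores the earlier measurements that the planned multilevel model uses, so it may overstate the loss. This stands too.
- **Bias.** The loss depends on calendar date, not on arm, so there is no evident between-arm bias. Maximum likelihood keeps late enrolees' pre-treatment, post-treatment and 6-month data. That is correct, but it does not supply the missing 12-month observations.
- **Reporting.** The Dropout section already reports losses by stage, including before the 12-month assessment. It has no category for visits that the end of data collection prevents, so separating them is a refinement.

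**Conclusion.** The point holds as an inconsistency between the Trial status and Procedure sections that should be fixed. If both dates stand, participants with a pre-treatment assessment in August to December 2025 reach 12 months after data collection has ended, and one of the three tested contrasts in each aim loses data.

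The calendar gap is certain from the text. Its size is not: about 18 participants under even accrual, about 10 to 33 over the range examined, and a 12-month power of about 73% to 81% at alpha 0.017 against 83% without the loss. These figures assume that both dates hold, that the full 20% attrition applies to the remaining participants, and that a two-sample comparison approximates the planned model.

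The harm is a moderate loss of precision at 12 months. The model, the outcomes, the allocation and the two earlier contrasts do not depend on these dates, so this is not a critical flaw.

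**What to change.** Reconcile the two sections in one of these ways:

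1. Run 12-month data collection to at least December 2026, plus whatever visit window the trial allows.
2. Set the last pre-treatment assessment no later than July 2025.
3. If neither date can move, state that participants enrolled after July 2025 are administratively censored before 12 months. Restate the expected 12-month n and power from the trial's actual accrual, not from the even-accrual illustration above. Report this loss separately from dropout in the participant flow.

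If one date is simply out of date, correcting it in the article and the registry entry is enough. The first option costs some further months of remote assessment, since follow-ups are by phone or video call, for the late enrolees (about 18 under even accrual). The second shortens the recruitment window by five months. The third costs only text and a recalculation.

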## Data Availability

Other than the authors and compliance with data-sharing agreements stipulated by the National Institutes of Health, no other entities have contractual agreements to access the final dataset.

